### Analysis methods

The original protocol stated: “All the data will be recorded and the questionnaires scored. Descriptive statistics including means and standard deviations will be reported as well as parametric and non-parametric tests as appropriate.”

Due to the small sample size, analyses will be largely restricted to descriptive statistics and elementary statistical tests.

Outcomes will be reported at baseline and 12, 24 and 36 months. Outcomes at 48 months will not be reported due to very low numbers.

For categorical outcomes, simple descriptive statistics will be reported.

For continuous measures we will formally test change using paired t-tests for the significance of the before/after difference of the main scales as specified above. For other scales and subscales we will calculate means and 95% CI at baseline and follow-up, showing baseline mean for both the whole sample and for the sample with data at the follow-up point.

Predictors of outcome: There are multiple hypotheses that could be made about whether individual demographic, physical or psychological factors relate to differences in outcomes, either by confounding or potentially more causally. Our design and study size mean that exploration of such hypotheses is not possible without high risk of chance findings. We will restrict analysis of predictors of outcome to two factors, birth registered sex and pubertal stage at baseline. We will restrict analysis to three continuous outcomes measured at baseline and 12 months. These outcomes were chosen as key outcomes across physical and mental health:

1. bone mineral density (BMD) in the lumbar spine
2. YSR total t-score
3. CGAS score

We will do this by linear regression of follow-up score on baseline score, adding each predictor separately to each model and considering the interaction of predictor with baseline score. If both factors appear to predict outcome, we will include these in a multivariable model and use backwards stepwise selection to identify the best predictive model.

We note that the nature of the patient group and their data are both unusual and highly sensitive, so that publication of findings may potentially identify individuals, particularly given the small sample size. We will consult with data protection experts to ensure that personal data are not disclosed.

Dissemination and Outputs

The findings of this study are of considerable public interest. They will first be published in a peer-reviewed international journal with the paper made open-access. They will be also presented at academic and practitioner meetings. In addition, the investigators will seek to share the findings more widely with patient groups and other stakeholders, using plain English.

The Tavistock will prepare a patient information sheet summarising findings for participants and families and circulate it to the participants and their GPs.

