| 1. Bone mineral density | DEXA scan report of bone mineral density in lumbar spine (L1-4) and hip:  Primary outcomes in spine and hip:  1. Bone mineral content (BMC)  2. Bone mineral density (BMD)  Secondary outcomes: calculated BMD z-score for age & sex, regression-adjusted for change in height z-score (height adjusted z-score: HAZ) | Annually | There is a strong relationship between bone strength, height and puberty. Normatively, BMC and BMD rise during adolescence due to the action of sex steroids on bone mineral accretion and because of height growth.  This will not occur if puberty is suppressed, as height does not increase and because bone mineral accretion is not promoted by sex steroid. The expectation is therefore that during GnRHa treatment bone strength as measured by BMC and BMD will not fall during treatment – but that it will not increase as expected from age and height growth. BMD z-scores for age reflect population increases in bone mineral, therefore z-scores will fall if puberty is suppressed, although without any reduction in bone strength.  We hypothesise that there will be no change in absolute BMD nor in BMC. However we expect that BMD z-score will fall consistent with falls in height z-score i.e. that HAZ will remain constant. | Change in continuous measures of BMC, BMD and BMD HAZ at 12, 24 and 36 months.  Formal statistical testing will be restricted to change in BMC and BMD as primary outcomes. Means and 95% confidence intervals (95% CI) will be calculated for HAZ at each time point. |
| D. PSYCHOLOGICAL FUNCTION |  |  |  |  |

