| 1. Child Behavior Checklist (CBCL) and Youth Self-Report (YSR) | The Child Behavior Checklist (CBCL) (parent report) and Youth Self Report (YSR) (self-report) are measures of psychological functioning (aseba.org). Both provide continuous data/ t-scores for the total problem scale (a global index of functioning across all subscales). They also provide continuous data/ t-scores on the internalizing subscale (items which assess anxious/depressed, withdrawn-depressed, and somatic complaints) and the externalizing subscale (focusing on rule-breaking and aggressive behaviours). The CBCL is used for children aged 6 to 18 and consists of 113 questions. Both are scored on a three-point Likert scale (0=absent, 1= occurs sometimes, 2=occurs often). The time frame for item responses is the past six months.  Raw scores are converted for analysis to t-scores based upon broad age-ranges.  Higher scores indicate greater morbidity. | At baseline and again after around 12 months on treatment. | Normative data show an increase in CBCL internalizing scores (i.e. psychological distress) with age in early adolescence.[22] It is therefore likely that any improvements in psychological function with treatment are likely to result in smaller rises in distress with age, meaning that there will be no discernible change in psychological function over time in our cohort.  Previous data from the London service and internationally show high rates of psychological distress in young people with GID.[42] Thus our sample is a group in whom distress begins at levels higher than the general population, but who will also suffer from the normative increase in distress across the study period.  We therefore hypothesise there will be   1. no change in total problem t-scores 2. no change in externalizing or internalizing subscale t-scores   This is consistent with a potential reduction in distress due to treatment at a time when there is a developmental rise in distress. | We will use t- scores for comparison with normative published data:   1. total problems score 2. internalising subscale score 3. externalising subscale score   Change in total problems score will be tested. Change in internalising and externalising t-scores will be estimated by calculating mean and 95% CI. |

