| 3. Self-harm | This will be assessed by 2 questions in each of the CBCL (parent report) and YSR (self-report).  Item 18: I deliberately try to hurt or kill myself (self-harm)  Item 91. I think about killing myself (suicidal ideation)  For each question in both CBCL and YSR the responses are:  0=not true  1=somewhat or sometimes true  2= very true or often true  We will use these items to calculate a self-harm/suicide items score at each timepoint by sum of the 2 items in each of the CBCL and YSR, as published by other authors.[24, 25] This produces a scale from 0 to 4 for each question – with higher score indicating greater suicidality/self-harm thoughts and behaviour. |  | Self-harm rates in the general population in the UK and elsewhere increase markedly with age across early to mid-adolescence, from very low in <10 year olds to peak around age 16-17 years.[43-46] This is likely related to adolescent development, particularly cognitive development.  Self-harm is highly prevalent in young people with GID, similar to rates in young people with a range of serious mental health problems.[34]  Thus our sample is a group in whom self-harm begins at levels higher than the general population, but who will also suffer from the normative increase in self-harm across the study period.  We hypothesise no change in self-harm across the study. This is consistent with a reduction in the propensity to self-harm due to treatment at a time when there is a developmental rise in self-harm. | We will assess change by change in self-harm/suicide items score. This score combines all categories of self-harm and suicidal ideation, including intermediate and high categories of risk. This will be formally tested. |
| 4. Teacher Report Form | The Teacher Report Form (TRF) is the third element of the Achenbach ASEBA system, asking teachers similar questions to the CBCL (parents) and YSR (young person self-report). Attempts to obtain TRF data on participants were rarely successful as this relied on families organising completion and return of questionnaires. Sample size for the TRF are insufficient to report, therefore data are not available on this outcome. |  |  | Not assessed. |

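### Every formally tested outcome is hypothesised not to change, but the plan tests for a difference and does not require a confidence interval for the change, so a non-significant result cannot support the hypothesis

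*SAP*

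**What the plan says.** Under Analysis methods the rule is: "For continuous measures we will formally test change using paired t-tests for the significance of the before/after difference", applied to the main scales. The next sentence deals with the rest: "For other scales and subscales we will calculate means and 95% CI at baseline and follow-up". No interval is asked for on the changes that are tested.

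The Outcomes table identifies what is tested and what is expected:

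- **Bone (C.1).** The measures are BMC and BMD, described as "Primary outcomes in spine and hip". "Formal statistical testing will be restricted to change in BMC and BMD as primary outcomes". The hypothesis is: "We hypothesise that there will be no change in absolute BMD nor in BMC". Change is assessed at 12, 24 and 36 months.
- **CBCL and YSR total problems (D.1, D.2).** Both are tested, and both are hypothesised to stay the same.
- **Self-harm (D.3).** One score comes from the CBCL and one from the YSR, and they are formally tested. "We hypothesise no change in self-harm across the study".

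Rows D.1 and D.3 add that an unchanged score would fit with a benefit of treatment, because distress and self-harm normally rise at these ages.

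Timing is given in two ways. Row D.1 says "At baseline and again after around 12 months on treatment". Row D.2 mentions only baseline and follow-up, and row D.3 gives no timing. Analysis methods says of outcomes in general: "Outcomes will be reported at baseline and 12, 24 and 36 months".

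The text available states no significance level, no limit for an important change, no rule for reading a non-significant result and no multiplicity adjustment.

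**The concern.** A paired t-test takes zero mean change as its null hypothesis. It can give evidence against no change. Failing to reject the null does not give evidence for it, because the same result arises when the change is real and the sample is too small to show it. Here the hypothesis of interest and the null are the same statement for every tested outcome.

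The plan already gives an unchanged score a favourable meaning for distress and self-harm. A reader handed only a p-value above 0.05 could therefore take it as support for benefit, when the data might equally be compatible with a worsening that matters. The interval for the change would show this, and the plan asks for intervals only where it does not test.

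The opposite error is also open. With many tests and no lead time point, an isolated significant result may be chance, and the plan gives the reader no means of judging it.

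**Working it through.** The SAP text available gives no sample size, power or error rate, so there is no figure of its own to reproduce. Assumptions are marked.

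**1. Number of tests**

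- Bone: 2 measures × 2 sites × 3 visits = 12.
- Psychological: CBCL total, YSR total and two self-harm scores = 4 outcomes. One follow-up gives 4 tests; three follow-ups give 12.
- Total: 12 + 4 = 16, or 12 + 12 = 24.

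**2. Chance of missing a real change**

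Assumed: T-score SD 10 (the T metric) at both times, correlation r between them of 0.5 or 0.7, true mean change of 3 points, two-sided 0.05, and n pairs.

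- SD of the change = 10 × √(2(1 − r)), which is 10.0 at r = 0.5 and 7.75 at r = 0.7.
- Non-centrality = 3√n / SD of the change. At n = 40 this is 1.90 or 2.45, against a critical t of 2.02.
- The chance of non-significance follows from the non-central t with n − 1 degrees of freedom.
- 95% CI half-width = critical t × SD of the change / √n.

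| Pairs | Missed, r = 0.7 | Missed, r = 0.5 | CI half-width, r = 0.7 to 0.5 |
|---|---|---|---|
| 40 | 33% | 54% | 2.5 to 3.2 points |
| 25 | 54% | 70% | 3.2 to 4.1 points |
| 12 | 77% | 84% | 4.9 to 6.4 points |

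For the bone outcomes, the same calculation can be put in units of the SD of the change. A true change of 0.3 SD is missed 65% of the time with 30 pairs and 86% with 10. For 0.5 SD the figures are 25% and 71%.

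**3. Chance of at least one false positive if every no-change hypothesis is true**

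Assumed: each test at two-sided 0.05.

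- Independent tests: 1 − 0.95^16 = 56%; 1 − 0.95^24 = 71%.
- Equal correlation between all test statistics, by simulation: at 0.3, 47% for 16 tests and 60% for 24; at 0.7, 26% and 31%.
- A block structure (correlated within bone, within psychology and across visits, but not between the two domains) gives 32 to 50% for 16 tests and 41 to 63% for 24, depending on the strength of correlation.

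Positive correlation is built into the design. Visits share one baseline, BMC and BMD come from one scan, and the self-harm scores use items of the CBCL and YSR. The independence figures are therefore an upper bound, and roughly 26 to 60% is the fairer range.

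**The case against.** The best defence is that the plan nowhere says that a non-significant result confirms a hypothesis. It describes a small before/after study, keeps analysis mostly descriptive, and a difference test can properly reject no change. That is right. A reader might infer that the SAP adopts non-significance as its criterion for no change, but no sentence says so. The fault is that nothing states how such a result is to be read and that the interval is not required. Both are still needed.

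The plan also limits testing. Growth, safety bloods, height-adjusted bone z-scores, body image and gender dysphoria are not tested. CBCL and YSR subscales, CGAS and Kidscreen are only estimated. The 48-month visit is dropped because too few participants remain, and the risk of chance findings is used to restrict the predictor analyses. It would be unfair to say the authors ignored the issue. What is absent is a lead time point or adjustment for the tests that remain, and that statement rests on the text available, which is not the complete SAP.

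Three stronger readings should be resisted:

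- *A chance finding is more likely than not.* This holds under independence, which the design rules out. In the correlated scenarios for 16 tests, none clearly exceeds one half.
- *The plan commits itself to 24 tests.* The general sentence on 12, 24 and 36 months speaks of reporting, not testing. Sixteen is the firm count; 24 is a possible reading.
- *The latest visit will look the most reassuring.* Fewer pairs do mean more missed changes of a given size. But the true change may grow with time, and on row D.1 the psychological scores may not be tested at that visit.

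**Conclusion.** The point stands. For all eight tested outcomes, the plan pairs a no-change hypothesis with a test that can only count against it, and omits the interval that would let a reader judge how much change remains possible. This mismatch does not depend on any assumed number.

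Its size does. With SD 10 and r of 0.5 to 0.7, a true 3-point change goes undetected in 33 to 54% of studies with 40 pairs and 77 to 84% with 12. The numbers of pairs, the SD, r and the 3 points are illustrative and not taken from the SAP.

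Multiplicity is secondary. There are at least 16 tests, possibly 24, with a substantial but not overwhelming chance of a false positive: roughly 26 to 60% at an assumed 0.05, with 56 to 71% as the upper bound.

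**What to change.** In Analysis methods:

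1. Report the mean paired change with its 95% CI for every formally tested outcome, and state that p>0.05 is not evidence of no change.
2. Conclude no change only if the CI excludes changes judged important. Otherwise report a change where the CI shows one, or call the result inconclusive. Set the limits for each scale, including both self-harm scores and the bone measures, before the results are seen.
3. Make 12 months the only formally tested time point. This leaves 8 tests (upper bound for any false positive: 1 − 0.95^8 = 34%). Give 24 and 36 months as estimates with CIs.
4. Reconcile the CBCL and YSR timing in rows D.1 and D.2 with the general reporting schedule, and give the timing for self-harm.

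The limits need care. With a 5-point limit on the T-score, for example, a true 3-point worsening would still be declared no change 23 to 36% of the time with 40 pairs, under the same SD and r. If 3 points matters, 5 is too wide.

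The cost is some SAP wording and agreement on the limits. More outcomes will be reported as inconclusive, and the later visits will carry no p-values. An adjustment such as Holm is optional; if used, the plan should say how it relates to conclusions drawn from the intervals.

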| 8. The Utrecht Gender Dysphoria Scale (UGDS) | The GDS is a self-report measure used to assess the intensity of Gender Dysphoria. The questionnaire provides a total score in the form of continuous data/ a t-score for one main scale only.  The questionnaire is used for children and adolescents aged 12 years and over.  The questionnaire consists of 12 statements and answers are given on a five-point scale to indicate to what extent one agrees or disagrees (1= agree completely, 2 = agree somewhat, 3= neutral, 4 = disagree somewhat, and 5 = disagree completely). A maximum score of 60 can be obtained. There are two separate versions of the UGDS for assigned males (UGDS-M) and assigned females (UGDS-F)  Higher scores indicate greater morbidity. |  | As noted above, GnRHa treatment does not change the body but merely prevents further pubertal changes. GnRHa treatment is therefore unlikely to affect feelings of gender dysphoria.  Hypothesis: gender dysphoria does not change with GnRHa treatment | Change in t-scores for total scale will be estimated by calculating mean and 95% CI. No formal statistical testing will be undertaken. |
| 9. Social Responsiveness Scale | The Social Responsiveness Scale (SRS) (school form) is a quantitative measure of autistic traits and symptoms in 4–18 year olds. It includes 18 items. A total score is produced.[59] |  | Young people with GID have been described to have relatively high levels of autistic traits. This may affect the natural history of and response to treatments for GID. It is unclear whether autistic traits would influence response to GnRHa treatment.  The SRS is used here as a baseline assessment of autistic traits and as a predictor of outcome and NOT as an outcome measure itself. The SRS was assessed only at baseline and not at follow-up as it was not anticipated that scores would change. | Not applicable. |
| E. Satisfaction with treatment |  |  |  |  |
| 1. Satisfaction with treatment  2. Continuation of treatment | Satisfaction with treatment was assessed in semi-structured interviews 6-12 months after commencing treatment.  Whether young people and families wished to continue on treatment was assessed at each clinic visit | 6 and 12 months on treatment  Each clinic visit | No hypothesis appropriate. No baseline data available. | Descriptive proportions.  Descriptive proportions |
| F. Decisions made at end of GnRHa treatment pathway |  |  |  |  |

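### The predictor analysis allows up to 12 uncontrolled looks and leaves a factor that passes alone unadjusted for the other

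*SAP*

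**What the plan says.** The Predictors of outcome paragraph in the SAP's Analysis methods notes that many hypotheses could be raised and that, with this design and size, "exploration of such hypotheses is not possible without high risk of chance findings". It therefore sets limits: "We will restrict analysis of predictors of outcome to two factors, birth registered sex and pubertal stage at baseline". It also says "We will restrict analysis to three continuous outcomes measured at baseline and 12 months", namely lumbar spine BMD, YSR total t-score and CGAS.

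The method regresses the 12-month value on the baseline value. The factors are examined by "adding each predictor separately to each model and considering the interaction of predictor with baseline score". The next step is conditional: "If both factors appear to predict outcome, we will include these in a multivariable model". From that joint model the plan would then "use backwards stepwise selection to identify the best predictive model".

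The paragraph does not say what counts as appearing to predict, what criterion removes a term, how an interaction would be acted on, or whether stage is linear or categorical. The Outcomes table (row A.3, Pubertal progress) gives stage four levels, 2 to 5.

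Row D.9 of the same table says of the Social Responsiveness Scale: "The SRS is used here as a baseline assessment of autistic traits and as a predictor of outcome".

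**The concern.** The limits on factors, outcomes and time point are sensible, but the procedure inside them gives part of the protection back.

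- **Number of looks.** Each factor is examined on its own and again through its interaction with baseline. That interaction asks whether the baseline slope differs between groups, not whether the factor shifts the outcome. The SAP states no hypothesis about it.
- **Adjustment depends on the screen.** A joint model is fitted only when both factors pass. If one passes alone, no estimate adjusted for the other is planned. With two candidates, both fit in one model and no screening is needed.

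At stake are false predictors on outcomes that the plan calls key across physical and mental health, and a sex coefficient that may partly reflect pubertal stage, or the reverse.

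**Working it through.** The SAP gives no sample size, alpha, power or error rate for this analysis, so there is no figure of its own to reproduce.

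**Inputs from the SAP.** Two factors, three outcomes, one follow-up time, a main effect and an interaction per factor, stage in four levels.

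**Assumptions.** Two-sided 0.05 per look (0.10 as sensitivity); 25, 40 or 60 participants with paired data; stage linear or categorical (3 df); baseline–follow-up correlation 0.5; correlation 0.3 between outcomes.

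**1. Number of looks.** 3 outcomes × 2 factors × 2 terms = 12. Main effects only: 3 × 2 = 6.

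**2. Chance of at least one false positive, independent tests: 1 − (1 − α)^k.**

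| | k = 6 | k = 12 |
|---|---|---|
| α = 0.05 | 1 − 0.95^6 = 26.5% | 1 − 0.95^12 = 46.0% |
| α = 0.10 | 1 − 0.90^6 = 46.9% | 1 − 0.90^12 = 71.8% |

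Simulation at 0.05 with no true effects (1,500 runs per setting) gives 24–28% for main effects alone and 44–48% with interactions, across all three sample sizes and both codings. The independence formula is therefore a fair guide.

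**3. Contribution of the stepwise step.** It runs only if both factors pass for the same outcome. Under the null, with independent tests, that has probability 0.05² = 0.25% per outcome, and 1 − (1 − 0.0025)³ ≈ 0.75% over three outcomes. For main effects, backward elimination can only keep or drop factors that have already passed, so it cannot flag a new one. The inflation comes from the number of screens.

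**4. Attribution.** Simulation of one outcome with a true stage effect only (0.3 per stage; follow-up SD given baseline 0.87), applying the plan's rule to main effects at 0.05, 2,000 runs per setting. The ranges cover the three sample sizes and both codings.

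| Observed sex–stage correlation | Sex passes its separate screen | Sex in final model, plan's full rule |
|---|---|---|
| about 0 | 4–6% | 3–5% |
| about 0.3 | 7–15% | 3–6% |
| about 0.55 | 15–33% | 6–10% |

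In a single joint model of baseline, sex and stage, a false sex coefficient has p < 0.05 in 4.0–5.8% of runs, whatever the correlation.

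Worked line (n = 40, linear stage, correlation 0.55): sex passes its screen in 23.8% of runs. Sex passes and stage does not in 3.0%; both pass and elimination drops stage in 4.8%; both are kept in 0.4%. Final model: 3.0 + 4.8 + 0.4 = 8.2%.

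The Monte Carlo standard error near 5% is √(0.05 × 0.95 / 2000) ≈ 0.5 percentage points, so at correlations of 0 and 0.3 the full rule shows no clear excess over the joint model. A further run of the full rule gave about 2–8%, against 4–6% for the joint model.

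**5. What a joint model leaves.** Six coefficients still carry 26.5% unadjusted. Testing at 0.05/6 would bring this to 1 − (1 − 0.05/6)^6 ≈ 4.9%.

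**The case against.** The plan names the danger itself, restricts the analysis to two factors, three outcomes and one time point, and keeps it apart from the formal before/after tests. It also says: "Due to the small sample size, analyses will be largely restricted to descriptive statistics and elementary statistical tests". The interactions are only to be considered, so counting six interaction p-values is a reading of the text; checking whether slopes differ is standard when regressing on baseline. Both points stand. They are why 12 is an upper count and why the interactions may stay as a model check.

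Four stronger readings are tempting and not supported:

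- **Stepwise selection generates the chance findings.** It is conditional on both factors passing, almost never runs under the null, and mostly corrects misattribution when it does run. It can still drop the wrong factor (up to about 5% of runs).
- **Sex would be falsely credited in up to a third of studies.** That is the rate at the separate screen. Under the full rule it is at most about 10%, and only with a strong sex–stage association.
- **Sex and stage are confounded in this cohort.** The SAP gives no association between them.
- **The reported confidence intervals will be too narrow.** Selection can do this, but the SAP does not say what will be reported from the selected model, and no size was calculated.

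The SRS wording is a separate, minor matter. Row D.9 lists its assessment as not applicable, and no SRS analysis is specified.

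**Conclusion.** The concern holds in a limited form. The plan leaves a high and uncontrolled risk of chance findings: about 46% for at least one false positive if all 12 looks are taken at an assumed 0.05, against about 26% for six main effects. This depends little on sample size or stage coding.

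That a factor passing alone goes unadjusted follows directly from the wording. Its numerical effect is modest and rests on an assumed sex–stage association and an assumed stage effect: false retention of sex of 6–10% at a correlation of about 0.55, against 4–6% for a joint model, and no clear excess at 0.3 or below. The case for change is that one joint model is simpler, needs no undefined pass rule, and is safe whether or not the factors are associated. It should be made, but it does not call the main before/after analyses into question.

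**What to change.** In Analysis methods, replace the screening and selection text with one pre-stated model for each of the three outcomes:

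12-month score = b0 + b1 × baseline score + b2 × birth-registered sex + b3 × pubertal stage + error

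- Fix the coding of stage in advance, for example one linear term over stages 2 to 5 to save degrees of freedom.
- Report b2 and b3 with 95% CI whatever their p-values, and label them exploratory. The label is needed because six coefficients still carry about 26%.
- Delete the rule that makes the joint model conditional on both factors, and delete the stepwise selection.
- Keep the baseline interactions, if at all, only as a labelled model check.
- Reconcile the SRS row (D.9) with the two-factor restriction, for example by removing its description as a predictor.

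The cost is a few sentences and fewer models. Confidence intervals widen when the factors are correlated, by roughly 1/√(1 − r²) at the same residual SD: 1/√(1 − 0.09) ≈ 1.05 at r = 0.3 and 1/√(1 − 0.3025) ≈ 1.20 at r = 0.55. A single stage term also assumes a linear trend across stages.
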